**Methods:**

All patients presenting in the participating centres with knee pathology warranting joint replacement therapy will be considered for inclusion, an absolute indication for cemented fixation is the only exclusion criterium. Evaluation of clinical and radiographic performance (e.g. radiolucent lines) is done at 6 weeks, 6 months, 1 year, 5 years and 10 years after surgery using validated patient reported outcome measures. Cumulative revision rates are calculated after 5 and 10 years using Kaplan–Meier methods. Physical function is assessed with performance based measurements before and 1 year after surgery. Return to sports is assessed using the Tegner and University of California Los Angeles (UCLA) activity rating scale before and 1 year after surgery. Return to work is evaluated by inviting patients of working age to complete a short questionnaire 1 year after surgery. Psychologic factors are assessed using questionnaires for pain catastrophising, pain self-efficacy and mental health before, 5 years and 10 years after surgery. Preoperative psychologic scores are correlated to functional outcomes.

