### Main outcomes – revision rate, complication rate, alignment, radiolucencies and PROMs

The main outcomes are revision rate, complication rate and patient reported outcome measures (PROMs) at 1 year, 5 years and 10 years after index surgery (Table 1). Revision is defined as any alteration to the implanted knee (e.g. implantation, explantation or replacement) including at least one component. Revision is further divided into major revisions (exchange or explantation of metal components) and minor revisions (exchange of insert or placement of patellar prosthesis).

**Table 1 Tab1:** Study procedures and distribution of the different outcomes in the follow-up schedule

	Preoperative	6 months	1 year	5 years	10 years
Patient reported outcome measures	X	X	X	X	X
Return to sports and physical function					
Tegner / UCLA activity scale	X		X		
Performance based measurements	X		X		
Return to work			X		
Radiographic analysis					
Radiolucent lines		X	X	X	X
Alignment	X		X		
Psychologic factors	X		X	X	X

N.B. Patients are routinely seen at the 6 week follow-up mark in some of the participating centres, no study parameters are registered at this visit

Complications are represented by any adverse event related to the knee surgery arising in the postoperative period. Complications are either major (e.g. prosthetic joint infection, reoperation other than revision, bearing dislocation/spin-out, manipulation under anaesthesia, venous thrombo-embolism) or minor (e.g. superficial wound infection, delirium).

Alignment is assessed on long-leg full weight bearing bilateral conventional radiographs before surgery and at the 1 year follow-up mark according to the parameters proposed by Hadi et al. (Table 1) [21]. Alignment parameters that are assessed include: sagittal and coronal tibial angle (sTA and cTA); sagittal and coronal femoral angle (sFA and cFA); coronal tibio-femoral mechanical angle (cTFmA), coronal tibiofemoral anatomical angle (cTFaA). All radiographs are furthermore assessed for progressive radiolucent lines at all time points according to the Knee Society Total Knee Arthroplasty Roentgenographic Evaluation and Scoring System [22].

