### Secondary outcome – return to work

All patients of working age (18–67 in the Netherlands) are invited to complete questionnaires 1 year after the index surgery to determine (Table 1):Whether or not patients return to their (original) workHow long after the index surgery they returned to workWorking hours per weekPhysical job demands according to the US Department of Labor’s Dictionary of Occupational Titles (sedentary, light, medium, heavy, and very heavy) [38].

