### Statistical analysis

Sample size calculation was aimed at non-inferiority of the Attune knee compared to the LCS knee, the predecessor of the Attune. A non-inferiority margin of 1.5% was assumed. Survival data of the LCS was extracted from a meta-analysis on long-term survivorship studies of the LCS TKA (mobile bearing cemented and uncemented implants) [45]. Pooled 10 year survivorship of the LCS was 98.1% [45]. Based on α = 0.05, power (1-β) of 0.90 and both true proportion (p) and null hypothesis proportion (p0) of 98,1%, a sample size of *n* = 709 was calculated with a one-sided test [46, 47]. Taking drop- outs and death within 10 years into account (approximately 20–25%), we are aiming for inclusion of *n* = 900 knees.

All data will be collected in Research Manager (Cloud9 software, Deventer, Netherlands) and exported for analysis to SPSS Statistics 26.0 (IBM SPSS, New York, USA). Data is coded and the encryption key is stored on the local hospital server of the participating institution. Statistical analysis will be mainly descriptive. Baseline characteristics and results will be described as means with standard deviations (SD) or 95% confidence intervals (95% CI), medians with interquartile ranges (IQR) or frequencies with accompanying proportions. Revision rates will be calculated by use of Kaplan–Meier survival analysis and competing risk analysis, where death is considered a competing risk [48]. Multivariable Cox proportional hazard analyses will be performed to assess the influence of radiolucent lines and implant alignment on implant survival and hazard ratios (HR) with 95% CI will be calculated. Mixed model analysis for repeated measures will be used for assessment of change in PROMs scores during follow-up. Multivariate linear regression analysis will be used to assess the association of radiolucent lines, implant alignment and preoperative psychologic scores (PSEQ, PCS and PHQ-2) with PROMs after 1, 5 and 10 years after index surgery.

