Descriptive statistics is provided on the proportion of patients that return to sport, what kind of sports they do (and whether this has changed due to surgery), the frequency and time to restart sports after TKA (in weeks). Improvements in Tegner score, UCLA activity scale and PBMs will be assessed with paired T-tests (or Wilcoxons Ranks sum test in case of non-parametric distribution). Descriptive statistics is provided on the proportion of patients of working age that return to work, time to restart work, working hours per week and physical job demands.

For all analyses, the significance level is set at 5% (*p* < 0.05).

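### The return-to-work proportion is defined over patients of working age, not patients in paid work before surgery, and no preoperative work item is scheduled

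*Protocol article*

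**What the plan says.** The protocol article describes return to work in four places, and they agree with one another.

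- **Analysis.** The Statistical analysis section gives the measure: "Descriptive statistics is provided on the proportion of patients of working age that return to work". Time to restart, weekly hours and physical job demands are also to be described.
- **Who is asked, and when.** The section on return to work as a secondary outcome reads: "All patients of working age (18–67 in the Netherlands) are invited to complete questionnaires 1 year after the index surgery". The four listed items are return to the (original) job, time until return, hours per week and physical demand category.
- **Schedule.** In Table 1 the return-to-work row has a single mark, in the 1-year column. The Tegner/UCLA row and the performance-test row are each marked preoperatively and at 1 year.
- **Abstract.** The Methods paragraph gives the same timing: "Return to work is evaluated by inviting patients of working age to complete a short questionnaire 1 year after surgery".

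The Statistical analysis section also says: "Statistical analysis will be mainly descriptive". Baseline characteristics are to be reported, but the article does not list them. The Discussion says the results can serve to tell patients how likely they are to get back to work and sport.

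**The concern.** A proportion returning to work needs a denominator of people who had work to return to. The population named here is defined by age. Someone under 67 who retired early, receives disability benefit or was otherwise not in paid work belongs to that population but cannot enter the numerator in any meaningful sense. Each such patient can only lower the rate.

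The schedule makes this harder to repair afterwards. The other activity outcomes have a preoperative measurement and work does not. Whether a patient was employed before surgery, for how many hours and in how demanding a job would have to be reconstructed from memory a year later. None of the four listed items asks outright whether the patient was employed before surgery.

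At stake is how a counselling figure is read. The patient who asks about returning to work has a job. A rate over everyone aged 18–67 mixes the answer to that question with the employment rate of the cohort.

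**Working it through.** The article states no expected return-to-work rate and no employment share, so it has no figure of its own to reproduce on this point. Its only computed figure, 709 knees, concerns implant survival and is not involved.

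**Inputs**

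- Denominator as written: all patients of working age (Statistical analysis; age range from the return-to-work section).
- *w*, the share of those patients in paid work before surgery: not given. Assumed 0.50 to 0.90.
- *r*, the proportion of prior workers who return by 1 year: not given. Assumed 0.85, and varied from 0.70 to 0.90.
- Literal reading: a patient with no prior job stays in the denominator and contributes nothing to the numerator.

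**Formula**

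With *N* patients of working age, *wN* were working and *r·wN* return. The rate over all *N* is *r·wN / N = w·r*. The rate among prior workers is *r·wN / wN = r*. The dilution factor is therefore *w*, and the gap is *r(1 − w)*.

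**Results for r = 0.85**

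| Share working before surgery (*w*, assumed) | Rate over working-age patients (*w·r*) | Rate among prior workers (*r*) | Gap, percentage points |
|---|---|---|---|
| 0.50 | 0.50 × 0.85 = 42.5% | 85% | 42.5 |
| 0.70 | 0.70 × 0.85 = 59.5% | 85% | 25.5 |
| 0.90 | 0.90 × 0.85 = 76.5% | 85% | 8.5 |
| 1.00 | 85% | 85% | 0 |

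The reported figure would thus lie at about 43–77% instead of 85%.

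**Sensitivity to r**

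The lowest combination is 0.50 × 0.70 = 35% and the highest is 0.90 × 0.90 = 81%. Whatever *r* is, the relative loss depends only on *w*. It disappears only if nearly every working-age patient was employed before surgery, or if patients without a prior job are taken out of the denominator.

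**The case against.** The strongest reply is that the article never says patients without a job are counted as failures to return. Asking about return to the original work presupposes such work. A patient without it could be marked as not applicable and left out, in which case the dilution is zero. The age range may only define who receives the form, with the analysis sentence repeating the phrase loosely. Baseline variables are not listed in this condensed article, so employment might be among them. The outcome is secondary and descriptive.

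Much of this stands. A reader might infer that non-workers definitely count as non-returners and that the rate will be wrong, but the article does not settle their classification either way. What the reply does not remove is the population that the analysis sentence does name, which is set by age, and the absence of a preoperative mark for work in a table that has one for the other activity measures.

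Two further inferences are tempting and are not supported:

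- **The same fault in return to sport.** The sentence reads "Descriptive statistics is provided on the proportion of patients that return to sport", without saying that all patients form the denominator. Tegner and UCLA are collected before surgery, and patients are asked which sport they do and whether it changed because of the operation. Patients can therefore be restricted or grouped by prior activity.
- **Time to return biased short.** The article promises descriptive statistics on time to restart and does not say how non-returners are handled. A summary labelled as being among returners, shown beside the proportion returning, is a legitimate description.

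**Conclusion.** The point holds as a defect of definition and data collection. As written, the return-to-work proportion is taken over patients aged 18–67 regardless of prior employment, and on the schedule shown, prior work status can come only from recall at 1 year. Followed literally, the rate is multiplied by the share employed before surgery. The 43–77% range against 85% illustrates the possible size. It rests on two assumed inputs and on the literal reading, and it predicts nothing about this cohort.

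No hypothesis test, sample size or main outcome is affected. The point is worth acting on because the figure is meant to be usable in patient counselling and the correction costs little.

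**What to change.** 1. In the Statistical analysis section, define the return-to-work proportion among patients in paid work before surgery, and report separately how many working-age patients were not in paid work.
2. Add work status, weekly hours and physical job demand to the existing preoperative questionnaire, with a matching preoperative mark for work in Table 1.
3. For patients already operated on, add an explicit 1-year recall item on whether they were in paid work before surgery, with the same hours and demand questions. Identify these as recall data in the report.

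The cost is a few extra questionnaire items at time points that already exist and one sentence of analysis text. The denominator will be smaller, so the estimate will be less precise, and patients already included will contribute recalled instead of prospective baseline data.

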### Data monitoring

The coordinating site (Spaarne Gasthuis) is responsible for data monitoring. Due to a very low additional risk the study brings, the medical ethics committee concluded that no data monitoring committee is necessary. All (serious) adverse events related to the implant are reported by the coordinating site to the medical ethical committee within 7 (serious adverse events) or 15 (adverse events) days.

## Discussion

Mode of implant fixation, cemented or uncemented, remains heavily debated among knee surgeons. Advantages of uncemented fixation include shorter surgery time and prevention of cement wear [49, 50]. Fear of aseptic loosening remains the main source of criticism for uncemented fixation [51]. High-level evidence fails to appoint superiority over both modes of fixation [50, 52–56], but registry and observational data slightly favours cemented implants in terms of durability [51, 52, 56]. One of the main drawbacks of registry studies is the fact that older uncemented implants (with known design flaws or absence of porous hydroxyapatite or tantalum coating) often skew reported survival of all uncemented implants [52, 56–60]. The current study can further contribute to this burden of evidence and determine long-term durability of the newest uncemented implant design in a large population.

Even though a highly successful procedure, a substantial group of patients remain dissatisfied after their TKA [61–65]. Besides distinct surgery specific factors affecting knee pain (e.g. severe malalignment, instability, infection, loosening), psychologic factors are known to play an important role in the perception of one’s artificial knee joint [66–70]. The current study can provide insight in the long-term impact of preoperative pain behaviour in a large population undergoing TKA, possibly predicting dissatisfaction. Interventions to modulate these pain believes before replacing the affected joint might provide useful in maximizing patient satisfaction after TKA [71].

There are several challenging aspects in the design of the current study. Minimizing loss to follow-up can prove difficult. Due to the highly successful nature of TKA, patients may not be willing to return for a clinical visit 10 years after surgery. Another deterrent to follow-up may be the high number of outcome measures recorded. Digital options for collection of the primary outcome measures (revision rate, complication rate and PROMs) can provide useful in this aspect and maximize data collection. The multicentre design always introduces bias due to the heterogeneity of surgical environment and hospital-specific factors. This is minimized by standardized surgical procedures and regulations already in place in all orthopaedic clinics (by the Dutch Orthopaedic Society). Nonetheless, a multicentre design also allows for generalisability of results and provides robust external validity for European health care environments. Furthermore, the role of industry funding should be considered as a possible source of bias for our study. However, the current study is investigator-initiated (i.e. protocol was constructed before the industry knew of its existence) and the role of the industry is as a funding body only. Therefore, there was no influence on methodology and there will be no influence on the results or their interpretation.

In conclusion, the current multicentre prospective observational cohort study aims at reporting the long-term clinical outcomes of a novel uncemented knee system. We furthermore attempt to provide information on return to work and sports, utilizing validated outcome scales supplemented with performance based measurements as a proxy for physical performance (as recommended by Witjes et al.) [31]. This information can be used to inform patients of their chances to return to sports and work after TKA. Finally, we also seek to shed light on the role of pain behaviour and mental status in the long-term patient satisfaction after TKA.

## Data Availability

The final dataset will only be accessible by qualified researchers from the coordinating site. The data is not available due to the lack thereof in this stage of the study.

## Abbreviations

TKA: Total knee arthroplasty
PBM: Performance based measurments
PROM: Patient reported outcome measure
EQ5D: EuroQol 5D
KOOS: Knee injury and osteoarthritis outcome scale
FJS-12: Forgotten joint score
NRS: Numeric rating scale
AKPS: Anterior knee pain scale
CFB: Change from baseline
PSEQ: Pain self-efficacy questionnaire
PCS: Pain catastrophizing scale
PHQ-2: Patient health questionnaire
